### Phase 2: Effectiveness evaluation of the app-based intervention

#### Intervention description

Participants in the intervention arm will receive app-based intervention. Each of them will be required to download the app and register as a user consequently, their accounts information, e.g. account name, email address used for registration will be collected. Four disciplines will be taken into account during the intervention period: (1) Interaction: at least once interaction will be required between the user and the app per week (e.g., sexual risk behavior report). (2) Non-stigmatization: a supportive atmosphere including social, behavioral, and psychological support will be built, and all contents will be presented without sense of discrimination. (3) Motivation encouragement: design and development of the app, information offered by the app will be in line with users’ needs, willingness and preferences so as to inspire their using motivation and maintain their adherence of the intervention. And two methods, health behavior goals setting according to the user’s sexual risk behavior, and exchange for free condoms with points earned by using the app regularly will be involved as incentive approaches to increase individual’s motivation of behavior change. (4) User-experience-centric: the app-based intervention will be user-oriented and we lay emphasis on user experience from aspects of interface and function modules as well.

#### Control group

For the control arm participants, each of them will be asked to build connection with the researcher through Wechat, the most widely used instant massaging app in China. They will receive usual care including free brochures of health information and free counseling services whenever they need. All of the participants will be promised of the confidentiality throughout the process.

#### Participant follow-up

All of the subjects in control and intervention arms will attend four visits, one at baseline for screening and enrollment, three at 6-, 12-, 18-month respectively to assess their sexual and other health behaviors (detailed below). Any subject gets HIV infected during the whole study period will be referred to professionals for timely treatment and withdrawn form the study. Information and psychological counseling services, positive sex tips and necessary links to care resources will be provided by the study staff.

Figure 1 is the Participant flow chart of the study.

**Fig. 1 Fig1:**
[figure not shown]
Participant flow chart

#### Data collection

Baseline data of all the subjects will be collected at the enrollment procedure. The measures including demographic information (*age, marital status, current occupation, educational level, income and sexual orientation*), sexual behaviors (*number of male and female sex partners, frequency of sex, sex role, commercial sex behaviors, sex with fixed and casual sexual partners*), and health-related behaviors (*consistent condom use with multi-type of sex partners, regular HIV testing, drug use experience and sexual transmitted diseases infection history*).

For the rest three times of data collection, sexual behaviors, health-related behaviors, and app user experience (*user experience, feedback and suggestions*) during the last 6 months will be involved in an electronic questionnaire. One version will be made into the app and be delivered every 6 months to intervention arm participants. Another without app user experience items will be delivered by Wechat to the ones in control arm.

Data of cost of the intervention and participants’ app use behaviors will also be collected. Direct cost involves cost of development, operation and maintenance of this app and worker cost, indirect cost consists of participants’ expenses due to their joining in the study such as time spending, cell phone internet data and traffic cost. App use behaviors will be collected through the management system which involves participants’ use frequency and time durance, information scanned, interaction times and frequency.

We use the electronic questionnaire to make sure that all of the items will be presented in a logical order and necessary answers missing will not be allowed. The participant will be offered a non-cash financial compensation as phone bills worth 20 RMB for compensation every time he complete the data collection.

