#### Outcome measures

Outcomes will be compared between intervention and control arms, and between different time points of each arm. The primary outcomes include HIV/STDs infection rates, relative risk of HIV/STDs infection, secondary outcomes include condom use rates, adherence to regularly HIV testing. The incremental cost is defined as per HIV infection case decreased according to the app-based intervention, cost of every 1% decrease of HIV/STDs infection, or every 10% increase of consistent condom use and adherence to regularly HIV testing. Another outcome is the app-based intervention mechanism (detailed below).

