#### Analysis of intervention outcomes

For intervention arm and control arm comparison, indicators of rates of HIV/STDs infection, consistent condom use, adherence to regularly HIV testing and sexual risk behaviors at baseline and at 6-, 12- and 18-month will be compared by using Chi-square test. And a COX risk model will be used for predicting HIV/STDs infection risks.

For the cost-effectiveness analysis, the total cost consists of direct and indirect cost mentioned above. Effectiveness covers the increased rates of consistent condom use and regularly HIV testing, the decreased rate of HIV/STDs infection, relative risk of HIV/STDs infection. A decision analytic model will be used to evaluate economic evaluation of the intervention. Using the estimated effectiveness and incremental cost of per HIV infection case decreased, every 1% decrease of HIV/STDs infection, every 10% increase of consistent condom use or adherence to regularly HIV testing, incremental cost-effectiveness ratio will be calculated.

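### STDs are recorded at baseline as infection history but at follow-up over the last 6 months, so a planned within-arm comparison from baseline can show a fall in STD rate with no intervention effect

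*Protocol article*

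**What the plan says.** All of the following is in the protocol article.

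- **Data collection, baseline.** The health-related items include "regular HIV testing, drug use experience and sexual transmitted diseases infection history". The sexual behaviour items are "number of male and female sex partners, frequency of sex, sex role, commercial sex behaviors, sex with fixed and casual sexual partners". No look-back is given for any of them.
- **Data collection, follow-up.** The three later collections are described separately: "For the rest three times of data collection, sexual behaviors, health-related behaviors, and app user experience" for the period "during the last 6 months will be involved in an electronic questionnaire". The 6-month limit is attached to these three collections only.
- **Recruitment.** Blood is taken at enrolment for HIV testing. No STD test is named.
- **Outcome measures.** "The primary outcomes include HIV/STDs infection rates, relative risk of HIV/STDs infection". The same section states: "Outcomes will be compared between intervention and control arms, and between different time points of each arm".
- **Analysis of intervention outcomes.** A sentence that opens by referring to the comparison of the two arms names HIV/STD infection first among its indicators and ends: "adherence to regularly HIV testing and sexual risk behaviors at baseline and at 6-, 12- and 18-month will be compared by using Chi-square test". A baseline STD rate therefore stands in the same series as the rates at 6, 12 and 18 months.

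**The concern.** As described, the baseline item and the follow-up item measure different things. A history item counts infections accumulated over however long the man is asked to look back. A 6-month item counts only recent ones. Placed in one series, the first value is higher than the others for a reason unrelated to behaviour or intervention.

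HIV does not have this problem, because entrants must be HIV negative. The STD part of the primary outcome does. A before-after comparison within an arm could show a marked drop in STDs in both arms, and a reader could credit that drop to the app or to usual care. The cost-effectiveness outcomes include a cost per 1% decrease in HIV/STD infection, and the article does not say whether that decrease is between arms or over time. If it is over time, the same artefact would enter there.

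Drug use has the same pattern (experience at baseline, last 6 months later), but it is not a named outcome.

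**Working it through.** **Figures in the plan.** The article gives no STD prevalence, incidence or baseline look-back, so there is no figure of its own to reproduce on this point. The sample size does not enter: 2 × ((1.960 + 1.282)/0.25)² ≈ 336 per group, as stated, and it depends on no recall window.

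**Step 1: what each collection measures.**

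| Item | Baseline | 6, 12, 18 months |
|---|---|---|
| STD infection | history, length not stated | last 6 months |
| Drug use | experience, length not stated | last 6 months |
| Condom use, HIV testing, sexual behaviour | window not stated | last 6 months |

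Only the first two rows have baseline wording that points to a longer period. The third row is silent.

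**Step 2: size of the artefact for STDs.** Assumptions, none of them from the article: a constant STD hazard λ per year, no intervention effect, no change in behaviour, and a baseline look-back of T years.

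Proportion with any STD in a window of T years = 1 − exp(−λT).

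Artificial fall = [1 − exp(−λT)] − [1 − exp(−0.5λ)].

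Example with λ = 0.05 and T = 5: baseline 1 − exp(−0.25) = 0.2212; follow-up 1 − exp(−0.025) = 0.0247; fall 0.1965, or 19.7 points.

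| λ per year | 6-month rate | 1-year look-back | Fall (points) | 5-year look-back | Fall (points) |
|---|---|---|---|---|---|
| 0.02 | 1.0% | 2.0% | 1.0 | 9.5% | 8.5 |
| 0.05 | 2.5% | 4.9% | 2.4 | 22.1% | 19.7 |
| 0.10 | 4.9% | 9.5% | 4.6 | 39.3% | 34.5 |

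Falls are taken from unrounded values. With T = 0.5 the fall is 0 at every hazard.

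**Step 3: would it be declared significant?** Take 400 men per occasion, a two-sided 5% test, and the two occasions as independent samples. With a 1-year look-back, the artificial fall is significant with probability about 0.21, 0.44 and 0.72 for the three hazards. With a 5-year look-back the probability is close to 1. These are rough figures: the same men are measured twice, the expected 20% loss to follow-up is ignored, and the article names no test for the within-arm comparison.

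**Step 4: effect on the randomised comparison.** Both arms get the same baseline items, before randomisation, and the same 6-month window afterwards. The artefact is equal in expectation in the two arms, so it cancels from any between-arm contrast at 6, 12 or 18 months. Comparisons among the three follow-up visits also use one window and are unaffected.

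**The case against.** The strongest reply is that the Data collection section is a condensed list of topics, not the questionnaire, and that recall periods are commonly left to a fuller document. For condom use, HIV testing and sexual behaviour this stands: nothing shows that the baseline window differs. For STDs it stands only in part. The article itself uses the word history at baseline and attaches the 6-month limit to the later collections alone, which is more than silence.

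Second, the STD outcome may not come from this item. Eligibility requires willingness to report HIV/STD test results, and the app has a module for uploading them. That is possible, but the article does not say that either source supplies a baseline STD rate. The app also reaches only the intervention arm, after baseline data have been collected.

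Third, the sentence on time points does not name baseline and could be met by 6, 12 and 18 months alone. That is literally correct. Yet the analysis section lists a baseline rate first in the series, and nothing excludes it from the within-arm comparison.

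Fourth, a reader might infer that the Chi-square tests compare time points. They do not: the sentence concerns comparison of the arms at each time. The Cox model concerns infection risk, and nothing in the article ties it to the baseline history item.

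Fifth, a reader might infer that a history item is useless as a baseline covariate. It is not. A covariate need not share the outcome's window, and prior STD history is a valid prognostic variable.

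Finally, the hazards and look-backs are assumed. That is true, and the result should be read as a range.

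**Conclusion.** The point holds for the within-arm comparison of STD rates from baseline to follow-up, and no further. If history covers more than 6 months, which is its ordinary meaning but is not defined in the article, and if the baseline STD rate comes from that item, then the planned comparison shows a fall in both arms with no effect. Under assumed hazards of 0.02 to 0.10 per year, the fall is about 1 to 5 points for a 1-year look-back and about 9 to 35 points for a 5-year look-back.

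Three stronger readings are not supported. The article does not show that all baseline behaviour values are on a different scale; for most items the window is simply unstated. It does not make the fall certain, since that depends on the two conditions above. And the randomised comparisons at 6, 12 and 18 months are not biased, so the trial's main evidence on the app is intact. The mismatch deserves correction because it touches a primary outcome in a comparison that the article says will be made.

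**What to change.** 1. **Data collection:** ask the baseline STD and drug use items over the last 6 months, worded as in the follow-up questionnaires. For consistency, state the same window for baseline condom use, HIV testing and sexual behaviour. Keep lifetime STD and drug history as separate items, for description or as covariates.
2. **Outcome measures:** limit within-arm comparisons from baseline to items asked over the same 6-month window, and state that STD history will not be compared with a 6-month STD rate.
3. **Analysis of intervention outcomes:** make clear that the baseline STD rate in the series is the 6-month item.

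If baseline data have already been collected with the history wording, omit the baseline-to-follow-up comparison for STDs and compare the arms at each follow-up visit.

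The cost is one or two extra baseline items and a few words in the text. No extra participants, visits or tests are needed, and the sample size does not change.

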#### Analysis of intervention mechanism

Correlation analyses between each aspect of participants’ app use behaviors (e.g. app use frequency and time durance, information scanned, interaction frequency) and effectiveness of the intervention will be performed. A causal path model will be built according to correlation analyses results and related theories. And a path analysis will be subsequently conducted so as to calculate the residual path coefficient and determination coefficient, define causal relationships between different variables, and thus explore intervention mechanism of the app-based intervention.

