## Discussion

In line with goals of implementation science, the study is going to develop a mobile phone app which comprises of behavioral, psychological and social services and for MSM, and implement a randomized controlled trial of HIV prevention intervention by using this app among MSM and evaluate effectiveness of the app-based intervention. The goals of the intervention are to provide MSM with health information, encourage their motivation of behavior change and promote their health skills.

It has been shown that apps are beneficial to self-management of people with chronic conditions, physical activity promotion among different age groups, and other health related behaviors [44–46]. There were systematic reviews pointed out that apps have great potential as tools for HIV prevention among MSM, and there were also studies on MSM’s acceptability and preferences of app-based. However, there is no randomized controlled trial targeting at MSM group with an app. This is the first study of its kind.

There are several strengths of the study. Mobile network is the combination of the Internet and mobile devices, and has the advantage of higher portability. The “always online” feature made it become a part of one’s daily life. Mobile phone can protect personal privacy and realizes point-to-point individualized intervention as well, which provide us with a better and accurate way to illustrate intervention mechanism. The long-term follow-up makes it possible to observe intervention effects with more persuasive results. And the cost-effectiveness analysis will help policy makers perform informed and practical decision-making.

As for the limitations of the study design, due to the open design we cannot mask the intervention, participants will be aware that they are in a HIV prevention intervention, which may introduce bias. Randomization allocation of participants into different groups can help achieve balance in sociodemographic characteristics. And researcher in charge of statistical analysis will be blinded to group allocation.

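### The mechanism analysis rests on app-use data from one arm, and no listed measure captures the knowledge, motivation or skills that the app aims to change

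*Protocol article*

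**What the plan says.** Four places in the protocol article bear on this.

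- **Outcome measures.** After the primary and secondary outcomes and the cost measures, the section adds: "Another outcome is the app-based intervention mechanism". The objectives at the end of the Background say that the mechanism will be explored, and Study design makes this a purpose of phase 2.
- **Discussion.** "The goals of the intervention are to provide MSM with health information, encourage their motivation of behavior change and promote their health skills".
- **Data collection.** Baseline covers demographics, sexual behaviors and health-related behaviors. The last group is itemised as "consistent condom use with multi-type of sex partners, regular HIV testing, drug use experience and sexual transmitted diseases infection history". For 6, 12 and 18 months the text reads "For the rest three times of data collection, sexual behaviors, health-related behaviors, and app user experience". The control version of the questionnaire differs in one respect: "Another without app user experience items will be delivered by Wechat to the ones in control arm". The app's management system also records "use frequency and time durance, information scanned, interaction times and frequency".
- **Analysis of intervention mechanism.** App-use behaviors are correlated with effectiveness. A path model is then built from those correlations and from theories that are not named, in order to "define causal relationships between different variables, and thus explore intervention mechanism of the app-based intervention".

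**The concern.** A mechanism analysis asks what lies between the intervention and the behavior. The article names three things that the app should change, but lists no measure of any of them. The variables it does name for the analysis describe how much of the intervention a man took up. That is exposure, not an intermediate step. The record of information viewed, for example, shows what was opened and not what was learned.

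The app combines education, goal setting, reminders and free condoms earned with points (Table 1 and Intervention description). If the trial is positive, the analysis as written could not say whether knowledge, motivation or skills carried the effect, or whether condom supply or reminders did. If it is null, the analysis could not separate an app that left its targets unchanged from one that changed them without changing behavior. The path coefficients would still be open to being read as causal, because that is the purpose the section states. A later analysis plan cannot repair this, since scores that were never collected cannot be recovered.

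**Working it through.** **1. Targets against listed measures.**

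| Stated goal (Discussion) | Listed measure, both arms | Nearest item, app arm only |
|---|---|---|
| Health information | none | record of information viewed (exposure) |
| Motivation | none | frequency of use and interaction (exposure) |
| Health skills | none | none |

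None of the three goals has a listed measure. The user-experience items are feedback on the app and are asked in the app arm only.

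**2. Who can contribute.** App-use records exist only in the app arm, so the 400 control men of 800 add nothing to the correlations that are named. Condom use, partner number and HIV testing are listed for both arms. They could stand between arm and infection, but the mechanism section does not plan this.

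**3. The plan's own figure.** Sample size and calculation gives α = 0.05 two-sided, power 0.9, effect size 0.25 and 336 per group. Reading 0.25 as a standardized mean difference (the article does not define it), n = 2 × ((1.960 + 1.282)/0.25)² = 336.2, which matches. With 400 enrolled and 20% lost, 400 × 0.8 = 320 per arm remain.

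**4. What a measured target could detect (illustrative).** An arm difference of 0.25 SD on a target score has 88.4% power at 320 per arm (t test). If the baseline score correlates 0.5 with follow-up (assumed), the effective difference is 0.25/√(1 − 0.25) = 0.289 SD and power is 95.4%. In 2,000 simulated trials with an assumed target-to-behavior slope of 0.3, a test requiring both links (arm to target, target to behavior) to be significant rejected in 87.9% of runs when the whole effect passed through the target. It rejected in 5.1% when the same total effect bypassed the target, and in 5.0% when there was no effect. The simulation has no confounding of target and behavior.

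**5. What the planned correlation can separate.** Assumptions: app use has unit variance and correlates 0.6 with engagement; engagement raises the outcome by 0.3; the target score has unit variance and slope 0.3; residual variance is 1.

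- *Effect does not depend on amount of use.* Correlation = (0.6 × 0.3)/√(1 + 0.3² + 0.3²) = 0.18/1.086 = 0.166. This holds whether the app works through the target, works by another route, or does nothing.
- *Effect grows with use*, by 0.25 × 0.3 = 0.075 per SD of use. Covariance = 0.18 + 0.075 = 0.255. Outcome variance = 1.18 + 0.075² + 2 × 0.3 × 0.075 × 0.6 = 1.213. Correlation = 0.255/1.101 = 0.23, against 0.17 for an app that does nothing.
- *Effect grows with use and engagement does not confound.* Correlation = 0.075/√(1.09 + 0.075²) = 0.07, against 0.

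Under all of these assumptions the correlation is the same for the two routes. Whether it separates a working app from an inert one depends on dose-response and on confounding.

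**The case against.** The strongest reply is that only a condensed article is at hand. Its baseline list is worded as non-exhaustive, the app-use variables are given as examples, and the path model may draw on related theories, so the questionnaire may hold psychosocial items that are not shown. This stands as a limit on wording: the point concerns listed measures only. It does not remove the point, because the article itself states the questionnaire content by visit and names app use as the starting point of the mechanism analysis.

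Second, the authors may have meant a narrower question, namely which kinds of use go with benefit. The Background does link mechanism to collected behavioral data. That question is legitimate, but its answer is a dose-response description within one arm and not the causal account that the mechanism section promises.

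Third, a reader might infer that the trial cannot address mechanism at all, or that the planned correlation cannot tell a working app from an inert one. The documents support neither. Behavioral intermediates are collected in both arms, and the equal correlations in the working arise only when the effect is independent of amount of use and engagement drives both use and outcome.

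Fourth, a mediation model has its own weakness. Target scores are not randomised, so confounding of target and behavior can bias it. This stands, and the fix must allow for it.

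**Conclusion.** The point holds in limited form. Mechanism is a listed, exploratory outcome, and the analysis described for it names only app-use variables that exist in one arm. None of the three stated goals has a listed measure in either arm. The analysis can therefore relate amount and type of use to outcome within the app arm. It cannot show whether the app changed its targets relative to control, or whether such a change carried an effect.

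The primary and secondary comparisons are untouched, so this is a worthwhile low-cost improvement rather than a threat to the trial's main conclusions. The conclusion rests on comparing the sections and not on the simulation. The figure of about 88% for detecting mediation is illustrative: it assumes a slope of 0.3, no confounding of target and behavior, and that the undefined effect size of 0.25 is a difference in SD units on a score not yet chosen.

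**What to change.** 1. **Data collection.** Add the same short HIV-knowledge, motivation and skills (self-efficacy) items to the baseline, 6- and 12-month questionnaires of both arms. Scores at 6 and 12 months then precede behavior at 12 and 18 months.
2. **Analysis of intervention mechanism.** Make the main analysis a mediation model in all randomised men: arm, then target score at 6 or 12 months, then condom use and testing at the next visit. Adjust for baseline score and baseline behavior. Report it as exploratory, with a sensitivity analysis for mediator-outcome confounding.
3. **If no items are added**, use condom use, partner number and testing at 6 or 12 months as intermediates toward later infection, and state that precision will be limited if infections are few.
4. **App-use correlations.** Keep them as a description of engagement in the app arm, and do not present them as causal mechanism.

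Cost: about 10 to 15 items, a few minutes per participant, on electronic questionnaires that already go to both arms, plus one model and its sensitivity analysis. No extra visits, staff or participants are needed. The downside is slightly more response burden.

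### With a 6-month recall at follow-up and a visit-by-visit test, the 18-month STD rate read literally covers only months 12 to 18, and a missed window is not recovered by the next questionnaire

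*Protocol article*

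**What the plan says.** All places are in the Protocol article.

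- **Data collection, baseline.** The health-related behaviours collected at enrolment include "regular HIV testing, drug use experience and sexual transmitted diseases infection history".
- **Data collection, follow-up.** The same label is carried to the three later rounds with a fixed look-back: "sexual behaviors, health-related behaviors, and app user experience (*user experience, feedback and suggestions*) during the last 6 months will be involved in an electronic questionnaire". The intervention arm gets the questionnaire in the app, the control arm by Wechat.
- **Participant follow-up.** After baseline there are visits, "three at 6-, 12-, 18-month respectively to assess their sexual and other health behaviors". Men who become HIV-infected are referred and withdrawn.
- **Outcome measures.** "The primary outcomes include HIV/STDs infection rates, relative risk of HIV/STDs infection". No period is attached to the rate. Outcomes are compared between arms and also between time points within each arm.
- **Analysis of intervention outcomes.** Infection rates stand in one list with condom use, HIV testing and "sexual risk behaviors at baseline and at 6-, 12- and 18-month will be compared by using Chi-square test". A Cox model for infection is added.
- **Other routes for results.** Inclusion criterion 5 requires willingness to report HIV/STD test results to the researcher (both arms). Table 1 gives the app a module for uploading such results (intervention arm only).

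**The concern.** A 6-month look-back suits condom use and partner behaviour, which are states of a period. A newly acquired infection is different: a prevention trial wants to know whether it happened at any time after randomisation. When the same recall and the same visit-specific test are applied to both, the 18-month STD figure answers for the last third of follow-up.

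Two things are at stake. The first is what the final primary rate means: a man with an STD at month 3 and none later is a case at 6 months and a non-case at 12 and 18. The second is ascertainment. A man with an STD at month 9 who misses the 12-month questionnaire and returns at 18 months is asked about months 12 to 18 and truthfully answers no. An analysis plan can choose to add windows together, but it cannot recover an answer to a question that was never put.

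**Working it through.** **The plan's own figures.** The sample-size section is the one place where an assumed infection rate might be found. With α = 0.05 two-sided, power 0.90 and effect size 0.25, the two-means formula gives 2 × ((1.960 + 1.282)/0.25)² = 336.2, which matches the stated 336 per group. The effect size is thus a standardised difference and carries no STD rate. Every rate below is an assumption.

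**Do the windows cover the trial?** Visits at 6, 12 and 18 months, each with 6-month recall, give 0–6, 6–12 and 12–18. They adjoin. For a man who completes all three, their union covers the whole 18 months, so a cumulative count is possible.

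**Share of ever-infected men seen in the last window.** Let p be the risk per 6 months, constant and independent between windows. Cumulative 18-month risk is 1 − (1 − p)³, and the share is p / [1 − (1 − p)³].

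| p per 6 months | Cumulative, 18 months | Share in months 12–18 |
|---|---|---|
| 1% | 3.0% | 33.7% |
| 5% | 14.3% | 35.1% |
| 10% | 27.1% | 36.9% |
| 20% | 48.8% | 41.0% |
| 30% | 65.7% | 45.7% |

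**Uneven risk.** If men differ in their rate (gamma-distributed, mean m infections per 6 months, shape k), the window risk is 1 − (1 + m/k)^(−k) and the cumulative risk is 1 − (1 + 3m/k)^(−k). For k from 1 down to 0.25 the share is 36–40% at m = 0.05, 39–45% at m = 0.10 and 44–52% at m = 0.20.

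So the interval and cumulative rates differ by a factor of about 2 to 3 (1/0.52 = 1.9; 1/0.34 = 2.9).

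**One missed questionnaire.** With two of three windows known, the share of ever-infected men identified is [1 − (1 − p)²] / [1 − (1 − p)³]: 67% at p = 1%, 68% at 5%, 70% at 10%, 74% at 20%.

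**Power, for illustration only.** Assume a halved hazard in the app arm, so its 6-month risk is q = 1 − (1 − p)^0.5; 320 evaluable men per arm (400 × 0.8); a two-sided 5% test of two proportions.

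| p (control) | 18-month rates if interval only, control vs app | Power | Cumulative rates, control vs app | Power |
|---|---|---|---|---|
| 3% | 3.0% vs 1.5% | 0.24 | 8.7% vs 4.5% | 0.59 |
| 5% | 5.0% vs 2.5% | 0.37 | 14.3% vs 7.4% | 0.80 |
| 8% | 8.0% vs 4.1% | 0.55 | 22.1% vs 11.8% | 0.94 |

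**Which reading does the text favour?** The list of comparisons runs "at baseline and at 6-, 12- and 18-month will be compared by using Chi-square test". Baseline, where nothing can have accumulated since randomisation, stands beside the later visits, and infection stands beside condom use. Within-arm comparison between time points also fits visit-specific rates. No sentence says that infections are summed. The literal reading is therefore interval, but the text does not exclude the other.

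**The case against.** The strongest objection is that the article never says the 18-month rate uses the 18-month questionnaire alone. The windows adjoin, infections found at 6 and 12 months enter their own comparisons, and a Cox model on first infection would use all of them. Whether a rate is interval or cumulative is a detail that a condensed article may leave to the full protocol or analysis plan. This stands against a firm claim that the plan counts only months 12 to 18, or that it discards earlier events. It does not answer the recall rule, which is a stated data-collection choice.

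Four further points on that side are right and limit what may be inferred.

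- **HIV as a lasting state set against a look-back for STDs.** A reader might infer this mixture, but seroconverters are withdrawn, and whether they count at 18 months is not stated.
- **A missed window as never ascertained.** Inclusion criterion 5 provides for result reporting in both arms. What is lost is ascertainment by questionnaire.
- **A missed window as never imputed.** The intention-to-treat section imputes missing endpoints by EM, repeated with multiple imputation, and does not confine this to month 18. A missing 12-month value can be filled, although a filled value is a prediction and not an observation.
- **The source of STD data.** The STD item is named only in the baseline list. That it is carried to follow-up under the same label is likely but inferred.

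The upload module does not help even-handedly. It belongs to the app, so using it to close gaps would make ascertainment differ by arm in a trial whose participants know their allocation.

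**Conclusion.** The concern holds in a limited form. As written, the follow-up recall of 6 months, apparently covering STD infection, and the visit-by-visit chi-square together give an 18-month STD rate for months 12 to 18. That is about 34–37% of ever-infected men at a constant 6-month risk of at most 10%, and roughly 40–50% at higher or uneven risk. A missed questionnaire leaves a window that the next one does not recover. If no other source fills it, about 67–74% of ever-infected men with that pattern are identified (6-month risks of 1–20%).

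These sizes rest on assumed rates, because the article gives none. The article also does not say how many men will miss an intermediate visit.

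A reader might go further and say that the final comparison loses most of its power. The documents do not support that. The contrast in power exists only under the literal reading, with an assumed halved hazard, and its size depends on the rate: at 8% it is a fall from 0.94 to 0.55, about 41% of the power (0.39/0.94). No comparison is designated as the final primary one.

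The point deserves action because the recall rule has to be settled before follow-up data are collected.

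**What to change.** 1. **Questionnaire, both arms.** For HIV and STD diagnoses and test results, ask about the time since the last completed questionnaire and record the month of diagnosis. Keep the 6-month look-back for condom use and partner behaviour. The month also gives the Cox model an event date.
2. **Outcome definition.** State the primary HIV/STDs outcome as first newly reported infection from randomisation to 18 months, built from all visits and from the same sources in both arms. Count men withdrawn after HIV infection as events. Visit-specific rates can remain as descriptive or supporting results.
3. **Sources.** If app uploads are used, pair them with an equivalent route for the control arm, or leave them out of the primary outcome.

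The cost is one reworded questionnaire item and a sentence or two in the outcome definition, with no extra visits or tests. The downside is longer recall for men who missed a visit: 12 months instead of 6 after one missed questionnaire, and 18 after two.
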